### Outcome measurements

All outcome measurements will be collected via a secure, encrypted online survey service. Participants will be invited via e-mail to complete the online self-report measures, and up to two reminder e-mails will be sent if they do not respond to the initial invitation.

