To improve access and extend the range of available depression treatment options, Internet-based treatments could play a key role [16, 17]. Indeed, several Internet-based interventions have been developed and tested over the past decade and are making a considerable impact upon the field of mental health care delivery [18, 19]. As early as 2002, expert panels have recommended exploiting the Internet to deliver evidence-based psychological treatments to underserved populations [20], and recent systematic reviews and meta-analyses have confirmed that some such interventions, most of which are based on CBT-principles, are effective for a range of psychiatric symptoms and conditions, including depression and anxiety disorders [21–23]. However, this body of research has also been criticized: many trials are conducted solely online, without establishing contact with participants to verify identity and diagnoses, and they suffer from various methodological problems such as excessive attrition and lack of follow-up data [24]. Nevertheless, at least in some countries, including Sweden, the Netherlands, Australia, and the United Kingdom, Internet-based psychological interventions with robust evidence are finding their ways into national treatment guidelines and are increasingly integrated in routine care services for patients suffering from depression, anxiety, and other psychiatric conditions [18, 25, 26]. Despite the considerable promise and success of some Internet-based psychological interventions, though, they have rarely been applied to the treatment of depression and anxiety among PwE.

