	MINI^a^	PHQ-9^b^	NDDIE^c^	GAD-7^d^	DASS-21^e^	WSAS^f^	Subjective usefulness of the program	INEP^g^	Epilepsy symptom severity^h^	Medication adherence^i^	Health-related quality of life^j^	ESMS^k^
T0 baseline	X	X	X	X	X	X			X	X	X	X
T1 (3 months post-baseline)		X	X	X	X	X	X^l^	X^l^	X	X	X	X
T2 (6 months post-baseline)		X	X	X	X	X	X	X^m^	X	X	X	
T3 (9 months post-baseline)		X	X	X	X	X	X^m^		X	X	X	

^a^MINI Neuropsychiatric Interview

^b^Patient Health Questionnaire

^c^Neurological Disorders Depression Inventory for Epilepsy

^d^Generalized Anxiety Disorder questionnaire, 7 items

^e^Depression and Anxiety Scales

^f^Work and Social Adjustment Scale

^g^Inventory for the Assessment of Negative Effects of Psychotherapy

^h^PESOS and Liverpool Seizure Severity Scale (LSSS)

^i^Rief Adherence Index (RAI)

^j^QOLIE-10-P (Quality of Life Inventory in Epilepsy)

^k^Epilepsy Self-Management Scale

^l^Only patients in the intervention group

^m^Only patients in the control group

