### Sample size calculation and analysis

The sample size of this study is based on the expected difference on the primary outcome variable (depressive symptom severity), between the intervention group and the control group at T1 (three months). Based on a power of at least 0.80 in a two-tailed test and an alpha of 0.05, randomization of 200 subjects (100 per group) will be sufficient to show an effect-size of *d* = 0.50 (moderate effect), anticipating an attrition rate of maximally 20% at T1, a rate that has been achieved in several previous trials [29–32]. With an anticipated sample size of 160 (2 × 80) completers at T1, power of .88 would be achieved for a moderate effect size of *d* = 0.50. Based on previous research by this group [27–29, 32], the assumption of achieving a moderate effect appears realistic. This power calculation is based on the assumption that an even randomization procedure (50:50) will be used.

Analyses will conform to recommended methodological standards, as specified by the CONSORT statement [93]. Specifically, both intention-to-treat and per-protocol analyses will be conducted, using appropriate methods such as linear mixed-models, which are widely used in this field and have been recommended because of their capacity to handle missing data appropriately [94, 95]. It is anticipated that attrition rate at post-treatment will be below 20%, given previous trial experiences [29, 31, 32]. Additional analyses will be performed to examine the potential influence of confounding variables on changes in the primary outcome (e.g., initial differences in symptom severity or treatment utilization).

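### After one invitation and up to two reminders for the whole T1 battery, no further attempt to obtain the primary PHQ-9 is described; one final PHQ-9-only request could recover some scores at little cost

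*Protocol article*

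**What the plan says.** Under Outcome measurements, the protocol article names one collection route for all outcomes, an online survey reached through an e-mail invitation, and adds that "up to two reminder e-mails will be sent if they do not respond to the initial invitation". A participant can therefore receive up to three e-mails per assessment. No shortened form, PHQ-9-only request or other contact mode is described.

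Table 1 (Recruitment and assessment) places the PHQ-9 in the same T1 assessment as the NDDIE, GAD-7, DASS-21, WSAS, epilepsy symptom severity, medication adherence, quality of life and ESMS. The usefulness items and the INEP are added at T1 with the footnote "Only patients in the intervention group".

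Under Sample size calculation and analysis, the authors plan 100 per group, "anticipating an attrition rate of maximally 20% at T1", and state: "With an anticipated sample size of 160 (2 × 80) completers at T1, power of .88 would be achieved". Missing data are to be handled by linear mixed models.

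**The concern.** The T1 PHQ-9 is the primary endpoint, and T1 is the only follow-up at which the intervention arm has used the program and the control arm has not (Recruitment and assessment). Controls get access after three months, so a control score from T2 or T3 cannot stand in for a missing T1 score.

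The primary score is nevertheless requested under the same rule as the whole battery. The battery is longer in one arm, and participants know their allocation (Study design), so non-response could differ by arm. A mixed model gives valid estimates if data are missing at random given what was observed. For someone who never answers after randomization, the only PHQ-9 on file is the baseline one. At the planned maximum loss, up to 40 of 200 primary scores (20% of 200) would be absent. Obtaining some of them is safer than modelling their absence.

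**Working it through.** **Inputs from the article.** Two-sided alpha .05 and power of at least .80; 100 per group, 1:1; d = .50; at most 20% attrition at T1; 80 completers per group; stated power .88. **Not in the article:** the share of non-responders who would return a PHQ-9-only form. This is an assumption, and the full range of 0% to 100% is shown.

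**Step 1: the plan's own figure.** Completers: 100 × (1 − .20) = 80 per group. Normal approximation: d × √(n/2) − 1.96 = .50 × √40 − 1.96 = 3.162 − 1.960 = 1.202, which gives power .885. The two-sample t test (noncentral t) gives .882. The stated .88 reproduces. The t test needs 64 per group for .80 power; 64/.80 = 80 randomized per group, so 100 per group exceeds the requirement. Power stays at or above .80 until about 36% attrition (64 per group, .802).

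**Step 2: battery length at T1.** Columns marked in Table 1 for both arms: PHQ-9, NDDIE, GAD-7, DASS-21, WSAS, epilepsy severity, adherence, quality of life, ESMS = 9. Intervention arm only: usefulness and INEP, so 9 + 2 = 11. Counting PESOS and LSSS separately makes it 10 and 12.

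**Step 3: power if a final short form recovers a share f of the missing** (equal loss in both arms, d = .50, t test). At 20% attrition, n per group = 80 + 20f:

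| f (assumed) | n per group | power |
|---|---|---|
| 0% | 80 | .882 |
| 10% | 82 | .889 |
| 25% | 85 | .900 |
| 50% | 90 | .916 |
| 100% | 100 | .940 |

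At 50% recovery the standard error of d falls from √(2/80) = .158 to √(2/90) = .149, about 6%.

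If attrition were 40% (assumption, twice the plan's maximum), power would be .775 at 60 per group. Recovery of 10%, 25% or 50% would give 64, 70 or 80 per group and power .802, .836 or .882.

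**Step 4: bias.** Let δ be the amount by which the arm difference among missing participants departs from what the model implies. The approximate bias is the missing share × δ. The documents give no δ. Each 0.1 SD of departure adds 0.02 SD of bias at 20% missing and 0.01 SD at 10% missing. With δ = 0.3 SD (assumption), bias is .20 × 0.3 = 0.06 SD with no recovery, .18 × 0.3 = 0.054 at 10% recovery, .15 × 0.3 = 0.045 at 25%, and .10 × 0.3 = 0.03 at 50%. This supposes that those still missing depart as much as those recovered. If the hardest to reach differ most, the reduction is smaller.

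**The case against.** The strongest reply is that an invitation with two reminders is an ordinary rule, and that question order, partial saving and last-resort contact are details a condensed article leaves to the full protocol. That stands as far as it goes: nothing here is a contradiction, and the full protocol may contain further retention steps. The contact rule itself, however, is stated, and it can be improved as stated.

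Several stronger readings are tempting and are not supported:

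- **The primary outcome is given up, or anyone who does not finish the battery is lost.** The article does not say that partly completed surveys are discarded, nor that the PHQ-9 comes late. It is the first self-report column in Table 1, although survey order is not stated.
- **The battery is too long for these participants.** Everyone randomized has already completed the T0 online assessment, which has the same nine self-report columns as the control-arm T1. The two extra intervention-arm columns concern use of the program, which controls have not had by T1. Length also cannot deter someone who never opens the e-mail.
- **The article admits the problem.** The Background remark that "they suffer from various methodological problems such as excessive attrition and lack of follow-up data" describes other trials. This one adds a telephone diagnostic interview and follow-up to nine months.
- **The trial is underpowered because of attrition.** The planned loss is already in the sample size, and the stated power is correct.

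One objection changes the remedy. A late request could bring in control scores after the waitlist has opened and so dilute the T1 contrast. A fixed window that closes before access is released meets this.

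It also stands that the calculations assume equal loss in both arms. They do not measure how far arm-dependent non-response would distort the result.

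**Conclusion.** The point holds as an optional, low-cost improvement, with low confidence because only the article is available. After up to three e-mails, no further attempt to obtain the T1 PHQ-9 is described, and a control score missed at T1 cannot be obtained later under the same conditions.

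The gain in power is modest: about 1 to 3 percentage points at 10% to 50% recovery of a 20% loss, and about 6 points if everyone is recovered. The better reason is reduced reliance on the missing-at-random assumption in an unblinded comparison. The size of that benefit depends on a recovery rate and a departure from the model that the documents do not give.

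**What to change.** - Put the PHQ-9 first in the T1 survey, ahead of any arm-specific items, and keep partial answers, if this is not already done.
- After the second reminder, send one final automatic e-mail with a PHQ-9-only form, on the same schedule in both arms.
- Fix a T1 window that covers this last request and closes before control participants are given access. The article places both T1 and release at three months, so the window should be stated relative to the release date.
- Flag short-form answers in the data set.

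**Cost.** Small survey set-up work and one more e-mail through the existing channel; research associates already invite participants (Conflict of interest, scientific integrity and independence). Some answers will arrive slightly later, and secondary scales stay missing for those who use the short form. A short form that participants come to expect might also lower completion of the full battery, which is a reason to offer it only after the second reminder.

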#### Primary outcome

The primary outcome, symptoms of depression, will be measured at T0, T1, T2, and T3 by the PHQ-9, a well-validated measure of depressive symptom severity [36, 37]).

#### Secondary outcomes

The following instruments will be used to assess secondary outcomes. Each instrument will be administered at T0, T1, T2, and T3, except of the Inventory for the Assessment of Negative Effects of Psychotherapy (INEP), the items regarding the subjective usefulness of the program and the Epilepsy Self-Management Scale (ESMS).The *NDDIE (Neurological Disorders Depression Inventory for Epilepsy* [83]*)* will be used as a secondary measure of depression symptom severity.
*GAD-7 (Generalized Anxiety Disorder questionnaire, 7 items)* [84, 85]: The GAD-7 is a well-validated measure of anxiety symptom severity. Originally developed to assess symptoms of generalized anxiety disorder, it has been shown to be a valid and reliable measure of anxiety severity more broadly conceptualized.
*DASS-21 (Depression and Anxiety Scales)* [82]: The DASS-21 is a valid and reliable brief questionnaire of depression, anxiety, and stress symptoms.
*WSAS (Work and Social Adjustment Scale)* [86]: The WSAS is a validated brief index of psychosocial impairment caused by depression (e.g., inability to work or pursue hobbies due to depression). The WSAS has been used in previous research by this group; psychometric properties have been found to be adequate [28].
*Subjective usefulness of the program:* measured by individually designed items, as in previous studies by this research group [28, 29, 32]. The items will be administered after using the intervention (intervention group: T1 and T2, control group: T2 and T3).
*INEP*: INEP is a reliable self-report instrument for assessing potential negative effects of psychotherapeutic treatment. A version that has been adapted to inquire about potential negative effects of Internet interventions is used here [87]. The INEP will be administered after 3-month using the intervention (intervention group: T1, control group: T2).
*Epilepsy symptom severity:* measured by validated measures (e.g., seizure frequency and severity; PESOS (Performance, Sociodemographic aspects, Subjective evaluation) [88] and LSSS (Liverpool Seizure Severity Scale) [89]).
*Medication adherence:* Measured by a brief, validated questionnaire, such as the 4-item Rief Adherence Index (RAI) [90].
*Health-related quality of life:* Measured with a validated questionnaire that assesses quality of life among PwE, the QOLIE-10 (Quality of Life Inventory in Epilepsy) [91].
*ESMS*: The ESMS is a reliable questionnaire that assesses frequency of use of epilepsy self-management practices [92]. The ESMS will be administered at T0 and T1.

Additionally, several items will be administered at the relevant time-points to assess specific demographic characteristics (e.g., age, gender) and illness-related parameters including:Frequency of interfering seizures (at T0):“Did you experience at least one seizure within the past year?” (yes, no)If no: “When did you last experience a seizure that interfered with your ability to pursue your normal activities?”“How often are you currently typically experiencing seizures that interfere with your ability to pursue your normal activities?” (no seizures, 1–5 seizures per month, 6–10 seizures per month, > 10 seizures per month)
Seizure frequency at subsequent time-points (at T1, T2, T3):“Did you experience at least one seizure within the past three months?” (yes, no)If yes: “Over the past three months, how many seizures have you experienced that interfered with your ability to pursue your normal activities?”
Current medication (at all time-points):“Which seizure medicine(s) are you currently taking? (please list)”

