**Methods/Design:**

This randomized controlled trial will include 200 participants with epilepsy and a current depressive disorder, along with currently at least moderately elevated depression (Patient Health Questionnaire (PHQ-9) sum score of at least 10). Patients will be recruited via epilepsy treatment centers and other sources, including Internet forums, newspaper articles, flyers, posters, and media articles or advertisements, in German-speaking countries. Main inclusion criteria are: self-reported diagnosis of epilepsy and a depressive disorder, as assessed with a phone-administered structured diagnostic interview, none or stable antidepressant medication, no current psychotherapy, no other major psychiatric disorder, no acute suicidality. Participants will be randomly assigned to either (1) a care-as-usual/waitlist (CAU/WL) control group, in which they receive CAU and are given access to the Internet intervention after 3 months (that is, a CAU/WL control group), or (2) a treatment group that may also use CAU and in addition immediately receives six-month access to the novel, Internet-administered intervention. The primary outcome measure is the PHQ-9, collected at three months post-baseline; secondary measures include self-reported anxiety, work and social adjustment, epilepsy symptoms (including seizure frequency and severity), medication adherence, potential negative treatment effects and health-related quality of life. Measurements are collected online at pre-treatment (T0), three months (T1), six months (T2), and nine months (T3).

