**Fig. 1 Fig1:**
[figure not shown]
Flow diagram of the randomized controlled trial

Consistent with the logic governing pragmatic RCTs, the trial will examine whether utilizing this program will improve depression outcome above and beyond the routine care patients are actually receiving [38, 40, 41]. Furthermore, particular attention will be paid to potential negative effects of the program, as assessed by a questionnaire. The trial thus aims to maximize external validity by contrasting the realities of current clinical care with the addition of an Internet intervention; it does not aim to maximize internal validity by selecting a maximally homogeneous patient group or introducing many other artificial control measures, such as narrow inclusion and exclusion criteria that do not reflect the clinical reality outside of trials [40].

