An outline of main content and program features is provided below. Each of five modules contains content that can be explored in briefer or longer individual sessions, depending on personal preferences. Depending on factors such as reading speed, interest to explore content in greater or lesser depth, and desire to listen to a greater or smaller number of audio recordings, each module can be completed in approximately 60 to 180 min. Thus, it would be possible to work through the entire program in as little as approximately five hours, or one could choose to spend much more time with it. As in other programs developed by our group [27–34, 48], there is no fixed or generic sequence in which modules must be completed, nor a minimum number of sessions that must be finished. Users are invited to freely explore the program and let themselves be guided within each section by the algorithm-driven sequences generated by the program. They are also informed that they can discontinue the program at any time if they feel that the program is not helpful or even harmful, and they are invited to contact the Principal Investigator, a licensed clinical psychologist, if they seek further help or advice. The purpose of such contacts would be only to provide information regarding treatment options, if clinically required, but not to provide therapeutic support. To define minimally sufficient usage, we are using the same algorithm we have used previously [32]: Having started at least four sessions and spent a total of least 60 min actively engaged with the program.

Program elements:
*Introductory module:* The introductory module provides an overview of the purpose, functions, and time-frame of the program. Patients are engaged in interactive sequences in which the CBT approach is briefly explained and in which their current and past medical and psychiatric history are explored. The introductory module addresses topics such as epilepsy onset and severity, types and intensity of current depression and anxiety symptoms, as well as exercise and nutrition habits. Patients are provided with a summary (“personal profile”) of their responses, and recommendations are made for further topics that patients may wish to engage with in subsequent sessions. The recommendation is made that patients use the program several times per week, as they see fit, for at least three months. They are informed that program access is provided for a six-month period.

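### INEP, the negative-effects questionnaire, has no unexposed comparison arm and does not cover months 4 to 6 of the intervention arm's access

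*Protocol article*

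**What the plan says.** Under Study design, in the text after Fig. 1, the article states that "particular attention will be paid to potential negative effects of the program, as assessed by a questionnaire". The Discussion counts the measurement of negative effects among the trial's strengths. The instrument is the INEP, described under Secondary outcomes: "A version that has been adapted to inquire about potential negative effects of Internet interventions is used here".

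Its timing is fixed in the same section: "The INEP will be administered after 3-month using the intervention (intervention group: T1, control group: T2". Table 1 agrees. The T1 entry for INEP carries the footnote "Only patients in the intervention group", the T2 entry is limited to the control group, and there is no entry at T3.

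The Abstract says that the intervention arm "immediately receives six-month access to the novel, Internet-administered intervention". The description of the introductory module repeats this for users: "They are informed that program access is provided for a six-month period". Controls receive access after three months. Recruitment and assessment identifies T1 as the point at which only the intervention arm has used the programme.

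**The concern.** The schedule does not match the emphasis that the article puts on negative effects. T1 is the only time with an unexposed randomised arm, and at T1 that arm does not answer the INEP. When controls do answer, at T2, they have had access themselves. A count of reported negative effects in one exposed arm cannot separate effects of the programme from the ordinary course of people enrolled with a depressive disorder and a PHQ-9 of at least 10. The error can go either way: background worsening may be counted as harm, or real harm may be dismissed as background.

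The second gap is in time. The intervention arm keeps access until month 6 and completes an online survey then, but that survey has no INEP. The programme runs without clinician guidance, so self-report carries more of the weight in detecting unwanted effects.

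**Working it through.** **1. The schedule, from Table 1 and Secondary outcomes**

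| | T1 (month 3) | T2 (month 6) | T3 (month 9) |
|---|---|---|---|
| INEP, intervention arm | yes | no | no |
| INEP, control arm | no | yes | no |
| Usefulness items, intervention arm | yes | yes | no |
| Usefulness items, control arm | no | yes | yes |
| PHQ-9, NDDIE, GAD-7, DASS-21, WSAS, seizures, quality of life | both arms | both arms | both arms |
| Has the control arm had access? | no | yes | yes |

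An unexposed comparison on INEP would need a yes for controls in the T1 column, and there is none. The text and the table do not contradict each other. This is a design choice that the article states, not a slip.

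**2. Coverage of the access period**

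The intervention arm has access for 6 months and answers INEP once, at month 3. Coverage is 3/6 = 50%. The control arm's INEP at T2 follows its own first three months of access, so it does not fill the gap. Usefulness is asked twice in each arm and negative effects once.

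**3. What one-arm INEP data can show**

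The article expects 200 × 0.80 = 160 completers at T1, that is 80 per arm, with power 0.88 for d = 0.50. This reproduces: Φ(0.50 / √(2/80) − 1.96) = Φ(3.162 − 1.96) = 0.885, or 0.882 with the t distribution. I therefore use 80 per arm below.

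If none of 80 intervention-arm respondents reported a given negative effect, the one-sided 95% upper bound on its rate would be 1 − 0.05^(1/80) = 3.7%. That is a ceiling within one arm. It says nothing about a difference from no access.

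**4. What the two-arm T1 data can show**

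The article gives no rate of worsening, so I assume 5 to 10% in each arm. The 95% CI half-width for a risk difference is 1.96 × √(2p(1 − p)/80):

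- p = 0.05: 1.96 × √(0.095/80) = 0.068, about 7 percentage points
- p = 0.10: 1.96 × √(0.18/80) = 0.093, about 9 percentage points

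Power with 80 per arm (two-sided 5%, rates again assumed) is 0.56 for 5% against 15%, 0.42 for 10% against 20%, and 0.89 for 10% against 30%. Only large differences would be detected reliably, so an estimate with its interval is more informative than a test.

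**The case against.** The strongest reply is that INEP is placed where it makes sense. The version used asks about effects of an Internet intervention, and people without access have nothing to report on. Timing is matched at three months of access in each arm, which fits the recommended minimum period of use and the 90 days of text messages. The article nowhere claims a between-arm comparison on INEP. This stands as a reason not to give the unchanged INEP to controls at T1, and the fix does not ask for that. It does not explain why the intervention arm, still with access, is not asked again at T2.

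A reader might infer more than the article supports:

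- **That the trial as a whole cannot attribute harm to the programme.** It can, at T1, on every outcome that both randomised arms complete: depression, anxiety, functioning, seizures and quality of life.
- **That months 4 to 6 go unobserved.** The intervention arm completes all these measures at T2, and the T2 seizure question looks back over exactly those three months. The article also commits to reporting every adverse event. Only INEP is absent.
- **That no analysis of harm is planned.** The Background announces exploratory analyses of negative effects and of seizure severity and frequency. Deterioration thresholds and table layouts may sit in an analysis plan that is not shown, so their absence here is no fault.
- **That INEP is restricted to people who used the programme.** Table 1 restricts it by arm, not by actual use.

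**Conclusion.** The point holds for INEP alone. The questionnaire to which the article ties its attention to negative effects is given once per arm and only after access. It has no unexposed randomised comparator, and it covers half of the intervention arm's access period. Its results can describe what participants report but cannot estimate an effect of the programme.

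No stated figure is wrong, and the primary analysis is unaffected. The remedy is a cheap improvement, not the repair of an error. The 50% follows directly from the schedule. The precision of 7 to 9 points rests on an assumed 5 to 10% worsening, on 80 completers per arm, and on worsening being unrelated to dropping out before T1. The last assumption is doubtful, since people who feel worse may be less likely to answer.

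**What to change.** 1. Add INEP to the T2 survey for the intervention arm. This raises coverage of that arm's access from 3 to 6 of 6 months.
2. State that INEP results are descriptive within-arm data and that the T1 intervention-arm and T2 control-arm results will not be read as a randomised comparison.
3. Base the between-arm statement on harm on T1 data already collected in both arms. Report the proportion whose PHQ-9 and GAD-7 deteriorate beyond a threshold set in advance, and the three-month seizure counts, with between-arm differences and 95% CIs. For seizures, compare the T1 counts themselves and not change from baseline, because the baseline item uses monthly frequency categories and the T1 item asks for a number over three months.

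The cost is one more short questionnaire for one arm, in a survey it already receives, and one more analysis table. No new T1 data are needed. If T2 has already passed for some participants, item 1 can apply only to those still to reach it, and the report should say so. Items 2 and 3 remain fully available.

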The goal of this parallel-groups, pragmatic RCT is to evaluate the extent to which a novel Internet intervention, used adjunctively to CAU, can contribute to improving symptoms of depression and anxiety, social-occupational functioning, physical health (epilepsy symptoms), medication adherence, and health-related quality of life, among PwE. Furthermore, the trial aims to evaluate the extent to which patients with epilepsy regard this intervention as a helpful and valuable tool. The primary focus of the software-based intervention is on facilitating depression reduction; hence, this is the target identified in the primary hypothesis.

It is hypothesized that, between baseline and three months, patients randomized to the intervention group will report greater reductions in depression, as measured by the Patient Health Questionnaire (PHQ-9), a well validated depression measure [36, 37], compared to patients randomized to the control condition. The goal of this pragmatic RCT [38] is to test the effectiveness of a novel Internet intervention on depression reduction among PwE over a period of three months, in comparison to a CAU/waitlist (CAU/WL) control group, which only receives access to the intervention after three months. Data will also be collected at six and nine months, which will allow us to examine the stability of intervention effects over time.

Secondary measures are administered to examine effects of the intervention on anxiety symptoms, stress symptoms, and depression-related psychosocial impairment, and it is hypothesized that participants assigned to the intervention group will show greater improvements in these respective measures over three months, compared to control group participants. Exploratory analyses will be conducted to examine potential negative effects of the intervention, effects on epilepsy symptom severity and seizure frequency, health-related quality of life, epilepsy self-management, and medication adherence. The subjective usefulness of the intervention will also be examined, and we expect that users will rate the intervention favorably, given that it was developed to address several of their epilepsy-specific needs and concerns.

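### The supplementary seizure items at T0 and at T1–T3 use different windows and scales, and the T0 bands skip from none to one per month, so these items give no matched baseline

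*Protocol article*

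**What the plan says.** The wording of the items is printed in the protocol article under Secondary outcomes, after the list of instruments.

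- **T0, any seizure:** "Did you experience at least one seizure within the past year" (yes/no). A patient who answers no is asked when the last interfering seizure was.
- **T0, frequency:** "How often are you currently typically experiencing seizures that interfere with your ability to pursue your normal activities", with the options "no seizures, 1–5 seizures per month, 6–10 seizures per month, > 10 seizures per month".
- **T1, T2 and T3, any seizure:** "Did you experience at least one seizure within the past three months" (yes/no).
- **T1, T2 and T3, frequency, if yes:** "Over the past three months, how many seizures have you experienced that interfered with your ability to pursue your normal activities", answered as an open number.

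The Background section lists "effects on epilepsy symptom severity and seizure frequency" among the exploratory analyses, and the Abstract names seizure frequency within the secondary measures. Table 1 schedules PESOS and LSSS at all four time-points as the measures of epilepsy symptom severity. The text under Secondary outcomes gives seizure frequency and severity as examples of what they cover.

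**The concern.** An outcome followed over time is normally asked in the same way at each visit. Here both parts of the question change after baseline. The yes/no window goes from 12 months to three. The frequency item goes from a banded typical monthly rate, with no defined recall period, to a count over a fixed three months.

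The T0 bands also have a gap where patients are likely to fall. The Inclusion criteria admit people with as little as one unprovoked seizure in 10 years, or with antiseizure medication within five years, so infrequent seizures are part of the intended population.

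At stake are the matched baseline for these items and the precision of any baseline adjustment. There is also a risk that someone later tabulates T0 against T1 and reads a change of window as a change in seizures.

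**Working it through.** The document gives no figure on this point to reproduce. Its power figure concerns the PHQ-9 and is not affected.

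**Step 1. Put the later counts on the T0 scale.** Inputs: the T0 bands and the three-month count, both from Secondary outcomes. Monthly rate = three-month count ÷ 3.

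| Three-month count | Rate per month | T0 band |
|---|---|---|
| 0 | 0 | none |
| 1–2 | 0.33–0.67 | no band |
| 3–15 | 1–5 | 1–5 |
| 16–17 | 5.33–5.67 | no band |
| 18–30 | 6–10 | 6–10 |
| 31 or more | 10.33 or more | more than 10 |

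The lowest non-zero band covers counts from 3 to 15, a five-fold range, so subtracting a T0 value from a T1 count is undefined. Counts of 1–2 and 16–17 cannot be placed at all.

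**Step 2. The gap on a yearly basis.** One per month is 12 per year. Between none and that lie 1 to 11 per year, or 1/12 = 0.08 to 11/12 = 0.92 per month. A patient with that many interfering seizures answers yes to the past-year item and must then choose either none or 1–5 per month (12–60 per year).

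**Step 3. Effect of the yes/no window alone.** The documents give no seizure rate, so this is an illustration over a range. Assume a steady Poisson rate of r seizures per year with no true change.

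- P(any in 12 months) = 1 − exp(−r)
- P(any in 3 months) = 1 − exp(−r/4)
- Apparent fall = exp(−r/4) − exp(−r)

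| r per year | 12 months | 3 months | Apparent fall (points) |
|---|---|---|---|
| 0.5 | 39.3% | 11.8% | 28 |
| 2 | 86.5% | 39.3% | 47 |
| 4 | 98.2% | 63.2% | 35 |
| 12 | 100.0% | 95.0% | 5 |

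The fall is largest where (1/4)exp(−r/4) = exp(−r), that is at r = (4/3)ln 4 ≈ 1.85 per year. The 47-point figure is therefore close to the maximum and should not be quoted alone. The fall arises equally in both arms.

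**Step 4. What remains usable.** From T1 onward both arms answer identical items, so the between-arm comparison at T1 does not depend on the T0 wording. A no to the T0 past-year item implies none in the preceding three months, so for those patients a matched zero is available. For the others, the T0 band is a coarse covariate.

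**The case against.** The strongest reply is that repeated measurement of seizures is assigned to PESOS and LSSS, which run at T0–T3. The items at issue are supplementary, listed with demographic characteristics, and have no column in Table 1. No section plans a T0–T1 change on them. The outcome is exploratory, the trial is randomised, and the window artefact is the same in both arms. The T0 frequency item concerns only interfering seizures, so a patient whose seizures do not interfere can truthfully answer none. Altering the form during recruitment would create two baseline versions.

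Most of this stands and limits the point. A reader might infer that the trial has no like-for-like baseline for seizures at all. The document does not support that: the wording of PESOS and LSSS is not shown, so their comparability can be neither assumed nor ruled out. A reader might also infer that the treatment comparison is biased, or that no baseline covariate exists. Neither follows, as step 4 of the working shows. Nor does the document make these items the main physical-safety signal. It names the INEP and the reporting of all adverse events, and the mismatch disables neither.

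The reply does not remove the mismatch or the gap in the bands. Both are in the printed items, and both can be closed cheaply.

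**Conclusion.** The point holds as a limited one about these supplementary items. Their windows and scales differ between T0 and T1–T3, and patients with 1–11 interfering seizures a year have no truthful T0 frequency option. No numerical change from baseline can be computed from them. What is lost is a matched baseline and some precision of adjustment, for an exploratory outcome. The primary outcome, the sample size and the T1 between-arm comparison are untouched.

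The mismatch and the gap follow from the printed wording and need no assumption. The apparent fall of 5 to 47 points rests on an assumed steady Poisson rate between 0.5 and 12 seizures a year. It shows what a T0–T1 table of the yes/no items could produce, and no such table is planned in the document.

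**What to change.** **Participants still to be enrolled:** at T0, add the three-month yes/no and count items already used at T1–T3, and keep the past-year item for description. Add a less-than-one-per-month option to the T0 frequency bands. Use the T0 three-month count as the baseline covariate when the arms are compared at T1. The choice of count model can be left to the SAP.

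**Participants already enrolled:** adjust for the T0 band, and do not report T0–T1 change from these items.

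**Cost:** one or two extra online items and one response option, plus two versions of the baseline form, because Trial status says recruitment is ongoing. The count covariate will be missing for those enrolled on the existing form, so the analysis has to allow for both versions. PESOS and LSSS stay as they are.
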